### Data collection procedure

This study has been approved by the Human Research Ethics Committees of Kano State and Jigawa State Ministries of Health.

Assessment of all participants will be carried out in four stages (at baseline, at 4 weeks, at 8 weeks, and at the end of the study). A comprehensive assessment of the participants will be conducted, where personal demographic information (age, height, weight, marital status, educational status) and PFRI-specific information (time since VVF repair, type/size of the VVF, amount of urine leakage) will be assessed at baseline; and functional status information (QoL, MH, SF, and PFS) will be assessed at baseline and after every four weeks up to 12 weeks. All the parameters will be assessed during follow-up after 6 months.

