Risk for developing PFRI depends on the site and type of fistula, as well as pelvic floor strength (PFS). Women with severe pelvic floor muscle (PFM) weakness are at risk of developing PFRI [21, 22]. According to Kayondo et al., type IIb fistulae are six times more likely to cause incontinence after successful repair than type I fistulae [22]. Also, women with circumferential fistula or larg fistulas are less likely to be continent after surgery [23]. PFRI also arises due to small bladder size/capacity following loss of the surface area of the bladder wall due to extensive fistula, neurologic damage, or due to the involvement of the urethral sphincter, especially if there is marked tissue loss and scarring [1, 8, 12]. Furthermore, PFRI occurs if there is loss of the sphincteric mechanism of the vesicourethral junction, and reduced bladder capacity or injury to the urethra [14, 20]. It has been reported that the risk of PFRI is 50% in women with minimal vaginal scarring and good bladder volume, while is 100% in women with reduced bladder volume and/or severe vaginal scarring [22–24]. Conservative interventions are the mainstay in the treatment of PFRI [11, 14, 20]; but unfortunately, supplementary surgery is prioritized over non-surgical options; the consequence of this is further deterioration of the condition [24]. It has however, been suggested that surgery should only be considered in persistent cases of PFRI or if the conservative treatment failed [12, 13].

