### Participants

Participants in this study will comprise all women with PFRI attending the obstetrics and gynaecology departments of MMSH and JGH. However, only women who meet the study inclusion criteria will be screened and randomized into the experimental (Paula Exercise Method) and control (Pelvic Floor Muscles Training) groups. Participants will be screened for eligibility by the researcher and the research assistants. Participants will be considered eligible if: they have had the PFRI for more than 3 months, to ensure that healing has taken place [1, 14]; they present with a 1 g gain in weight following a pad test; they consent to participate through a written informed consent; they are not above the age of 50 because as women age changes occur in the bladder and pelvic structures that can increase the risk of developing incontinence [36]; they have no faecal leakage; they have not had previous rectal surgery; they are not receiving any other alternative PFM rehabilitation at the point of recruitment; and urinary infection is ruled out because it affects the integrity of the pelvic organs [37].

After screening for eligibility, a cough test will be used to differentiate the type of incontinence. In the cough test, if urine leakage coincides with the cough, it is classified as stress incontinence (SI), however, if the leakage is delayed till after the cough, it is urge incontinence. No leakage after the cough signifies that it is overflow and functional incontinence [38].

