### Randomization

After screening the participants, and following baseline assessments, a computer-generated random allocation sequence will be used to assign the participants to either the intervention group (PEM group where they will receive PEM plus PFMT), or the control group (where they will receive PFMT only). To eliminate bias, the randomization will be carried out by a third party who is not aware of the study group. Assessment of outcome will be carried out by an experienced/trained researcher, who will be blinded to the type of intervention received by participants in each group. The study participants’ flow diagram is presented in Fig. 1

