### Outcome

A proforma will be developed by the researcher which will be used to document the demographic features (such as age, weight, height, blood pressure, address, type of incontinence, education status, and marital status) of all the participants as well as the pre, post and follow-up intervention findings of the study.

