## Data analysis

Microsoft Excel will be used to record all the data obtained before being exported to the Statistical Package for Social Sciences (SPSS). Descriptive and inferential statistics will be used to analyse the data. All study parameters will be summarized using descriptive statistics of frequency, mean, standard deviation, and percentage. Factorial ANOVA will be used to determine between-group differences/interactions in the study groups from the pre to the follow-up study period for PFS and UL among study participants. The Wilcoxon signed-rank test will be computed to determine differences between the pre, post and follow-up intervention for SF, ML and QoL scores in both the experimental and control groups. The independent t-test will be used to determine the difference in the post intervention PFS and UL scores between the experimental and control groups, while Mann–Whitney U will be used to determine the difference in the post intervention for SF, ML and QoL scores between the experimental and control groups. The magnitude of the differences between the groups will be determined by calculating the effect sizes. Missing data will be handled through multiple imputation. All analyses will be performed with probability set at 0.05 alpha level.

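### Fistula type and size are presented as determinants of continence and recorded at baseline, but the planned between-arm tests of urine leakage do not use them, which may cost some precision

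*Protocol article*

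**What the plan says.** All references are to the protocol article.

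- **Background** states that "type IIb fistulae are six times more likely to cause incontinence after successful repair than type I fistulae" and that "women with circumferential fistula or larg fistulas are less likely to be continent after surgery".
- **Data collection procedure** lists the fistula-specific items to be assessed at baseline: "time since VVF repair, type/size of the VVF, amount of urine leakage".
- **Participants** adds that "a cough test will be used to differentiate the type of incontinence", and the proforma described under **Outcome** includes "type of incontinence, education status, and marital status".
- **Randomization** says that "a computer-generated random allocation sequence will be used to assign the participants" and names no stratification factor.
- **Data analysis** fixes the tests. For urine leakage and pelvic floor strength, "The independent t-test will be used to determine the difference in the post intervention PFS and UL scores between the experimental and control groups". A factorial ANOVA over the study period is also planned for these two outcomes; its text mentions the study groups and the period and no other factor. Mann–Whitney U is used for the questionnaire outcomes.
- **Table 1** lists the baseline variables as age, weight, height, blood pressure, marital and educational status, and time since repair. Fistula type and size are not among them.

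**The concern.** The document argues that fistula anatomy matters for continence and plans to record it, and then names primary-outcome tests that leave it out. An independent t-test cannot take a covariate, so this is a stated choice of method and not only silence. The eligibility criteria do not restrict fistula type or size, so the sample may be anatomically mixed.

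If anatomy predicts leakage beyond the baseline pad weight, two things follow. Variation that could be explained stays in the error term, so the confidence interval for the primary comparison is wider than it need be. And if one arm happens to receive more of the severe anatomy, readers will ask whether that explains the result. An adjustment chosen only after the data are seen would be open to the charge of selection.

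**Working it through.** **Inputs.** Sample size: 166 women (83 per arm) before attrition, 182 (91 per arm) recruited. The document gives no figure for the prognostic strength of fistula type or size, so there is no planned figure to reproduce on this point. R² below means the share of residual variance in leakage, beyond baseline leakage, that fistula type/size explains. It is an assumption, shown from 0 to 0.20. Five covariate terms (q = 5) are also an assumption.

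**Step 1: is the unadjusted test valid?** Yes. In a simulation with 83 per arm and no treatment effect (20,000 runs), the unadjusted t-test rejected in 4.97% of runs at R² = 0.05 and 5.2% at R² = 0.20, with mean error about zero. Omitting the covariates neither inflates the type I error nor biases the estimate.

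**Step 2: how large can chance imbalance be?** For a binary factor with prevalence p (assumed) and 91 per arm, the SD of the difference in proportions is √(2p(1−p)/91).

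- p = 0.20: √(2 × 0.16/91) = 0.059; chance of a gap of 10 points or more about 9%.
- p = 0.50: √(2 × 0.25/91) = 0.074; chance of such a gap about 18%.

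This is ordinary sampling variation, already reflected in the unadjusted standard error. It is the same cost as the precision loss in Step 3 and must not be added to it.

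**Step 3: what would adjustment gain?** The ratio of adjusted to unadjusted standard error is √(1−R²) before the cost of estimating the terms. With that cost it is approximately √[(1−R²) × (N−3)/(N−3−q)], where N = 166 and q = 5, so the multiplier is 163/158 = 1.032.

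| Assumed R² | √(1−R²) | Ratio with five terms | Change in standard error |
|---|---|---|---|
| 0 | 1.000 | 1.016 | +1.6% |
| 0.05 | 0.975 | 0.990 | −1.0% |
| 0.10 | 0.949 | 0.964 | −3.6% |
| 0.20 | 0.894 | 0.908 | −9.2% |

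Break-even is where (1−R²) × 163/158 = 1, that is R² = 1 − 158/163 = 0.031. Below about 3% explained variance, five terms cost slightly more than they return.

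**Step 4: in terms of power.** With 83 per arm, two-sided α = 0.05 and 90% power, the detectable standardised difference is (1.960 + 1.282) × √(2/83) = 0.50. For an effect of that size, power with adjustment is Φ(3.242/ratio − 1.960): 89.1% at R² = 0, 90.6% at 0.05, 92.0% at 0.10 and 94.6% at 0.20. The plan's effect size of 0.3 is not used as a yardstick, because its metric is not stated and 166 does not follow from 0.3 read in SD units. That is a separate matter.

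**The case against.** The strongest reply is that nothing here is invalid. Randomised arms may be compared without adjustment, and a covariate list is commonly left to the analysis plan, which is not shown. The first part stands in full. The second stands only in part, because Data analysis names the tests, and an independent t-test leaves no room for covariates; an analysis plan that adjusted would depart from it. The factorial ANOVA is different: it could take fistula type as a further factor, although its description gives only group and period.

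A second reply is that the Background concerns the risk of becoming incontinent after repair, whereas every participant already has that condition. The document shows no link between anatomy and pad weight, or response to exercise, within this group. This also stands, and it is why the gain is given as a range that includes a small loss.

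A reader might go further and infer that chance imbalance biases the trial's result, or that time since repair and incontinence type should be adjusted for as well, across all outcomes. The document does not support these readings. Randomisation protects the test, as Step 1 shows. No passage ties time since repair or incontinence type to the outcome. Nothing links fistula anatomy to the sexual function or mental health scales.

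**Conclusion.** The point holds as an efficiency and interpretability improvement to the primary comparison. Fistula type and size are put forward as determinants of continence, are to be recorded, and are not used in the between-arm tests of urine leakage. The unadjusted comparison remains valid.

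The size is not known from the document. It ranges from a loss of about 1.6% in the standard error (R² = 0) to a reduction of about 9% (R² = 0.20), assuming five covariate terms, 166 women analysed, and R² counted beyond baseline leakage. A useful gain needs anatomy to explain clearly more than about 3% of that remaining variance, which is plausible from the mechanisms in the Background but not shown there.

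**What to change.** In Data analysis, prespecify the between-arm comparison of urine leakage as a regression on a scale suited to skewed pad weights, for example log-transformed or rank-based. The Sample size section reports that pilot leakage was not normally distributed. Adjust for baseline leakage and for fistula type/size in a few categories defined in advance, one of them for unknown.

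- Keep the unadjusted comparison as a sensitivity analysis.
- Treat time since repair and incontinence type as optional covariates, to be decided before data are seen.
- Do not impose this list on the secondary outcomes.
- Add fistula type/size to the baseline row of Table 1 so that it agrees with Data collection procedure. The proforma list under Outcome is illustrative, so its silence needs no correction.

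**Cost.** A change of wording on data already planned for collection, a few degrees of freedom, and some women in the unknown category, since recruitment draws partly on hospital registries where older records may lack the fistula type.

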### Randomization

After screening the participants, and following baseline assessments, a computer-generated random allocation sequence will be used to assign the participants to either the intervention group (PEM group where they will receive PEM plus PFMT), or the control group (where they will receive PFMT only). To eliminate bias, the randomization will be carried out by a third party who is not aware of the study group. Assessment of outcome will be carried out by an experienced/trained researcher, who will be blinded to the type of intervention received by participants in each group. The study participants’ flow diagram is presented in Fig. 1

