### Setting

All participants will be recruited from Murtala Muhammad Specialist Hospital (MMSH) and Jahun General Hospital (JGH) in Kano and Jigawa states of Nigeria respectively. The training will be conducted at the physiotherapy departments of the two institutions. The MMSH is a major health institution in Kano State; it is a specialist and referral centre to all hospitals in Kano State and its neighbouring states. It has a bed capacity of eight hundred and twenty six (826), thirty (30) wards and units, nine (9) operating theatres, fourteen (14) clinics, and a staff strength of 1656. Similarly, JGH is a state hospital located in Jahun local government area of Jigawa State. It provides quality health services to people in Jigawa State and the neighbouring states. It is a 300-bed capacity hospital with diverse clientele who receive treatment from the different clinical departments of the facility.

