### Sample size

The sample size of this study was estimated based on the findings of a pilot study. We conducted a pilot study to test the adequacy and feasibility of this protocol as well as to determine the sample size required for this study. The pilot study participants were recruited after being certified as eligible to participate using the specified study inclusion criteria. Recruitment was conducted by reviewing records of the outpatient urology clinic on a weekly basis. A total of 30 women with post fistula repair incontinence participated in this pilot study. The 30 subjects were randomly assigned into the two arms of the study resulting into 15 participants in each arm of the pilot study (Paula Exercise Method and Pelvic Floor Muscle Training groups). All participants were assessed at baseline before randomization and prior to the commencement of intervention, post intervention (outcome). The primary outcome of interest is Urine leakage. The programme was structured for 4-weeks of daily routine activities in both groups. The detail of urine leakage assessment is described later in the manuscript as the primary outcome measure.

In this pilot study the mean age of participants was 29.9 ± 9.4, the median Urine leakage score for PEM and PFMT was 4.53 g and 21.61 g respectively. We computed Mann Whitney U for the data because the data was not normally distributed. Result for an independent two groups non-parametric test indicated significance (*U* = 38.00,* p* = 0.020) with an effect size of *Ƞ*^2^ = 0.32.

Using the outcome of the pilot study and according to a power calculation to detect a between-group difference, of 0.3 effect size for two independent means Mann Whitney U in urine leakage (UL) with 90% power at α = 0.05, a total sample size of 166 was generated. This suggests a total of 83 participants in each group. A 10% attrition rate will be considered, therefore, 182 participants will be recruited giving 91 participants in each group. The recruitment of participants from the two hospitals would be accomplished by: involving the surgeons from the departments of obstetrics and gynaecology of both hospitals who are involved in performing the fistula repairs (in the recruitment); and reviewing hospital registry and subsequently contacting patients whose records are available through individual phone contacts.

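### No blocking or stratification by hospital is described for this two-hospital trial, and the stated urine-leakage t-test ignores hospital: a small, cheaply avoided loss of precision

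*Protocol article*

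**What the plan says.** The Setting section names two recruiting hospitals. Of the first, with 826 beds, it says "it is a specialist and referral centre to all hospitals in Kano State and its neighbouring states". Of the second it says "It is a 300-bed capacity hospital with diverse clientele". Training takes place in the physiotherapy department of each. Under the two intervention headings, women return at four, eight and twelve weeks to the hospital that recruited them.

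The Randomization section says that "a computer-generated random allocation sequence will be used to assign the participants to either the intervention group" or the control group, and that a third party carries this out. It mentions no blocks, strata or lists by hospital, and it does not say that allocation is unrestricted. The Sample size section expects that "182 participants will be recruited giving 91 participants in each group".

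The Data analysis section states: "The independent t-test will be used to determine the difference in the post intervention PFS and UL scores between the experimental and control groups". It also plans a factorial ANOVA of leakage and pelvic floor strength across study groups and time. No listed test is described with hospital as a factor, stratum or covariate.

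**The concern.** Hospital is known before allocation and is fixed for each woman. It may carry differences in case mix and in how training and the pad test are carried out. The protocol's Background ties post-repair incontinence to fistula type and size, scarring and bladder capacity, and a referral centre may see more of the difficult cases. That last step is inference, since no leakage or severity figures by hospital are given.

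A baseline factor that affects leakage does two things if neither the allocation nor the analysis uses it. Its distribution can differ between arms by chance, which moves the estimated treatment difference in an unpredictable direction. Its variance also stays in the residual, which widens the confidence interval. Both effects can be avoided almost without cost. What is at stake is precision and the ease of interpreting the result, not validity.

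**Working it through.** **Inputs from the protocol.** Two hospitals; 182 women, 91 per group; 83 per group evaluable for 90% power at alpha 0.05; 10% attrition; independent t-test for post-intervention leakage.

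**Inputs assumed.** The protocol gives neither the recruitment split nor a hospital difference. I take 50% to 80% of women from one hospital (60/40 for power) and a hospital difference h of 0.25, 0.5 or 1 within-hospital SD. Outcomes are treated as normal.

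**Step 1: the plan's own figure.** 166 × 1.1 = 182.6, taken as 182, or 91 per group. The 166 itself does not follow from an effect size of 0.3 read as a standardised mean difference: a two-sided t-test would need 235 per arm. That is a separate and larger matter. Here I use d = 0.503, the difference that 83 per arm detects with 90% power, so that the effect of hospital is judged at the power the plan intends.

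**Step 2: chance imbalance in hospital mix without stratification.** With 91 per arm, the number of women from one hospital in an arm is hypergeometric. The SD of the difference in shares is 2 × SD(count) / 91.

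| Share from one hospital | SD of difference | 95% limit (1.96 × SD) |
|---|---|---|
| 50% | 0.0743 | 14.6 points |
| 60% | 0.0729 | 14.3 points |
| 70% | 0.0683 | 13.4 points |
| 80% | 0.0592 | 11.6 points |

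At the 50% split, an imbalance at the 95% limit shifts the treatment contrast by 0.146 × h, which is 0.036, 0.073 or 0.146 SD for h = 0.25, 0.5 or 1. The shift is random in sign and averages zero.

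**Step 3: variance left in the error term.** With a 60/40 split, hospital adds 0.6 × 0.4 × h² = 0.24h² to a within-hospital variance of 1.

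- h = 0.25: 0.015/1.015 = 1.5% of the total variance
- h = 0.5: 0.06/1.06 = 5.7%
- h = 1: 0.24/1.24 = 19.4%

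**Step 4: power.** Evaluable women: 182 × 0.9 = 163.8, taken as 164, or 82 per arm. The unadjusted test works with d/√(1 + 0.24h²), which is 0.499, 0.489 or 0.452. The adjusted test keeps d = 0.503, less about one woman's worth of information for chance imbalance. Results are from the non-central t distribution and from a simulation (6,000 runs, unstratified allocation).

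| h | Formula: without → with hospital | Simulation: without → with hospital |
|---|---|---|
| 0.25 | 88.8% → 89.1% | 88.5% → 89.1% |
| 0.5 | 87.5% → 89.1% | 86.5% → 88.4% |
| 1 | 82.0% → 89.1% | 82.8% → 89.5% |

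The simulation error is about 0.4 points per figure. The gains are about 0.5, 1.5 to 2, and 6 to 7 points.

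**Step 5: validity.** In the same simulation with no treatment effect, type I error at h = 0.25, 0.5 and 1 was 5.3%, 5.1% and 4.9% without hospital, and 5.3%, 5.0% and 5.2% with it. The unadjusted test is sound.

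**Step 6: if allocation is stratified but the analysis is not.** I simulated exact balance within each hospital (20,000 runs). The plain t-test then becomes conservative, with type I error of 4.6%, 4.1% and 2.8%. Power with and without hospital is 89.1% against 88.8%, 89.0% against 87.9%, and 89.3% against 84.7%. The analysis term is therefore worth having under either reading of the allocation text.

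**The case against.** The strongest reply is that the allocation half rests on silence. Block sizes and stratification factors are often left to the full protocol, which is not shown, and covariates are often left to the analysis plan. A reader might infer from the singular wording that one unrestricted sequence serves both hospitals. The article does not say so. The pilot's even split of 15 and 15 fits restricted allocation somewhat better, since under simple allocation an exact split of 30 has a chance of about 14%. This stands: no allocation error can be asserted, only that no restriction is described.

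A reader might also infer that 91 per group is in doubt. If allocation were unrestricted, an exact 91/91 would have a 5.9% chance and one arm would range from 78 to 104 (95%). But a 78/104 split keeps 98.0% efficiency and moves power only from 89.6% to 89.0%. Arm size is not a reason to act.

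The hospitals differ in bed count and referral role. Nothing shows that they differ in leakage, and eligibility criteria and the pad test are common to both. This stands too, and is why h is given as a range.

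The objection fails on the analysis half. The independent t-test for leakage is named outright, and it has no place for hospital whatever the full protocol says about allocation.

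**Conclusion.** The point holds as a matter of efficiency. Two hospitals of different type take part, no blocking or stratification by hospital is described, and the stated leakage t-test does not use hospital. If allocation is unstratified, hospital mix may differ between arms by about 12 to 15 percentage points by chance. Using hospital in the analysis gains roughly 0.5 points of power at a 0.25 SD hospital difference, 1.5 to 2 at 0.5 SD, and 6 to 7 at 1 SD. The gain matters in practice only towards the upper end of that range.

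The tempting stronger reading is that hospital differences bias the comparison between arms. They do not: randomisation balances hospital on average, and type I error stays at about 5%.

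The figures assume normal outcomes, a 60/40 recruitment split and d = 0.503. The pilot leakage data were not normally distributed, so the SD-based gains are a guide to scale.

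**What to change.** Have the third party generate a separate list for each hospital, in permuted blocks of varying size, and state this in the Randomization section. Varying the block size makes the next assignment harder to guess for the trainers, who cannot be blinded.

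In the Data analysis section, include hospital in the between-arm analysis of urine leakage: as a factor in the ANOVA, or in a linear model that replaces the plain t-test. If leakage is analysed by ranks, use a van Elteren test stratified by hospital.

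If the full protocol already stratifies by hospital, only the analysis change is needed, together with a sentence in the Randomization section saying so.

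The cost is two lists instead of one and one extra model term. Sample size, visits and assessments stay as they are.
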